### Assessments and procedures

2.4

All study outcomes and corresponding assessment time points are presented in **Table 2**. The primary outcome is the change in HFC, as measured by magnetic resonance imaging, from baseline to 12 weeks post-intervention. Secondary outcomes encompassed: (1) anthropometric parameters; (2) body composition and abdominal fat; (3) cardiorespiratory fitness; (4) cardiometabolic biomarkers; and (5) Indicators of liver inflammation and fibrosis. Detailed measurement procedures are described below.

**Table 2 T2:** The study schedule.

Study phase	Screening	0 week	4 week	8 week	12 week
Informed consent	✓	–	–	–	–
Demographics	✓	–	–	–	–
Medical history	✓	–	–	–	–
Lifestyle counseling	✓	✓	✓	✓	✓
Medications report	✓	✓	✓	✓	✓
Physical and diet assessment	✓	✓	✓	✓	✓
Anthropometric assessment	✓	✓	✓	✓	✓
Randomization	✓	–	–	–	–
MRI-PDFF	–	✓	–	–	✓
Cardiometabolic biomarkers	✓	✓	–	–	✓
Liver inflammatory biomarkers	✓	–	–	–	✓
Body composition	✓	✓	–	–	✓
Cardiorespiratory fitness	✓	✓	–	–	✓
Quality of life	✓	✓	–	–	✓
Adherence	✓	✓	✓	✓	✓
AEs	✓	✓	✓	✓	✓

MRI-PDFF, Magnetic Resonance Imaging - Proton Density Fat Fraction; AEs, adverse events.

#### Primary outcomes

2.4.1

The primary outcome is the absolute change in HFC, quantified as MRI-PDFF, from baseline to 12 weeks. All MRI-PDFF measurements will be acquired using a standardized multi-echo gradient-echo sequence on the same 3.0T scanner (Magnetom Prisma, Siemens Healthineers, Erlangen, Germany), using an 18-channel body and a 32-channel spine phased-array coil, conducted by a single professional technician who is blinded to group allocation. A multi-echo 3D spoiled gradient-echo sequence (Volumetric Interpolated Breath-hold Examination-Based, VIBE) integrated within the Siemens LiverLab sequence will be performed under a single end-expiratory breath-hold. Typical acquisition parameters included: repetition time (TR)< 12 ms, six asymmetric echo times (TEs, e.g., first TE ~1.2ms, echo spacing ~1.2ms), flip angle ~3-6°, axial orientation, field of view covering the entire liver, and parallel imaging. PDFF maps will be automatically generated by LiverLab, which employs a multi-peak fat spectral model and corrects for T2-weight decay. The liver will be segmented using an artificial intelligence algorithm embedded in the assessment program. Segmentations with a goodness-of-fit exceeding 95% will be accepted after reviewing the images and reports.

#### Secondary outcomes

2.4.2

##### Clinical assessments

2.4.2.1

Height and weight will be measured using an electronic scale (DC-250, TANITA, Japan). Waist and hip circumferences will be assessed by trained nurses following standardized procedures, with participants standing in an upright position. Waist circumference will be measured at the midpoint between the lower margin of the last palpable rib and the top of the iliac crest, while hip circumference will be measured at the widest point over the buttocks. In addition, blood pressure will be measured according to the established clinical guidelines. Participants remained seated and at rest for a minimum of 5 minutes before assessment. Measurements will be obtained on the right upper arm using a validated automated sphygmomanometer with an appropriately sized cuff. Two successive readings will be taken at 1–2-minute intervals, and the mean value will be used for subsequent analyses.

##### Body composition and abdominal fat

2.4.2.2

Body composition will be assessed via dual-energy X-ray absorptiometry, which enables precise quantification of fat mass and lean mass distribution using dual-energy X-ray absorptiometry (Lunar Prodigy, GE Healthcare, USA). Participants will be required to fast for ≥8 hours prior to testing and keep a standardized supine position on the scanning table with limbs immobilized using foam supports. The upper extremities are abducted at 15°from the torso while maintaining full leg extension, ensuring optimal anatomical alignment for accurate cross-sectional analysis.

Concurrently with hepatic fat assessment, abdominal adipose tissue will be also quantified. A T1-weighted VIBE Dixon sequence will be performed, centered at the L4-L5 intervertebral disc level under a single breath-hold. Acquisition parameters are repetition time (TR) 4.3ms, dual echo times (TE1/TE2) 1.29/2.52ms, slice thickness 3.0 mm, voxel size 1.5 × 1.5 × 3.0 mm³, and flip angle 7°.

Image analysis will be performed using OsiriX software (Pixmeo SARL, Bernex, Switzerland). Five axial slices centered at the L4-L5 midpoint will be reconstructed. Subcutaneous adipose tissue (SAT) and visceral adipose tissue (VAT) areas will be manually delineated using region of interest (ROI) tools, and the mean area (cm^2^) across the five slices will be calculated.

#### Cardiometabolic indicators

2.4.3

After a 10–12 hour overnight fast, blood samples will be collected from participants by the clinical laboratory of Changhai Hospital following standardized protocols. A comprehensive panel of serum biochemical parameters will be assessed, including fasting glucose, insulin, glycated hemoglobin (HbA1c), total cholesterol (TC), triglycerides (TG), high-density lipoprotein cholesterol (HDL-C), low-density lipoprotein cholesterol (LDL-C). Insulin resistance will be evaluated using the homeostasis model assessment for insulin resistance (HOMA-IR) (19).

##### Indicators of liver inflammation and fibrosis

2.4.3.1

We quantified a range of biomarkers associated with liver inflammation and fibrogenesis, including, alanine aminotransferase(ALT), and aspartate aminotransferase (AST), adiponectin, cytokeratin-18 (CK-18), fibroblast growth factor-21 (FGF-21), procollagen type III N-terminal propeptide (PIIINP), ferritin, and tissue inhibitor of metalloproteinases-1 (TIMP-1). The degree of hepatic fibrosis will be additionally estimated using validated non-invasive indices, specifically the Fibrosis-4 index (FIB-4) (20) and the AST-to-Platelet Ratio Index (APRI).

##### Cardiorespiratory fitness

2.4.3.2

A treadmill-based maximal cardiopulmonary exercise test (CPET) will be performed in conjunction with indirect calorimetry to accurately measure peak oxygen uptake (VO_2peak_). After a 5-minute low-intensity warm-up and familiarization, participants underwent a graded exercise protocol with treadmill (h/p/cosmos sports & medical gmbh, Germany) and wearable metabolic system (Cosmed K5, Italy) using the modified Bruce protocol (21). The modified protocol incorporated two additional low-intensity stages at the beginning of the original protocol. This adaptation is specifically suitable for individuals with metabolic disorders. Therefore, the modified Bruce protocol enhanced test tolerability and safety while allowing for more accurate determination of VO_2peak_ in clinical populations with limited exercise capacity. During the incremental exercise test, participants’ exertion levels will be monitored using the Borg Rating of Perceived Exertion scale, for which standardized instructions will be provided prior to testing. Heart rate will be continuously recorded by heart rate monitor (Polar H10, Finland). Due to the compromised CRF commonly observed in this clinical population, a clear oxygen uptake plateau is often not achieved during the incremental exercise test. Therefore, the VO_2peak_ will be determined based on the attainment of at least two of the following criteria:1) Measured heart rate within 10 beats per minute of the age-predicted maximum (calculated as 207 - 0.7 * age in years); 2) Respiratory exchange ratio (RER) ≥ 1.10, and 3) Borg RPE score ≥ 18. Following the test, participants engaged in a cool-down period involving light walking or slow cycling until their heart rate returned to baseline levels. The testing will be conducted by a qualified exercise physiologist, and continuous access to medical support will be ensured throughout the procedure.

##### Dietary and physical activity assessment

2.4.3.3

At baseline, participants will be required to complete a 3-day dietary record (two weekdays and one weekend day) using a mobile application (BOHE Corporation, Shanghai) to assess their habitual energy intake. Based on this baseline assessment, a dietitian will provide standardized dietary guidance to ensure caloric stability. During the intervention, participants will use the same mobile application to record their dietary intake on three randomly selected days (two weekdays and one weekend day) every two weeks. If the calculated average daily energy intake deviates from the baseline level by more than 10%, the dietitian will provide immediate feedback to facilitate a return to habitual intake levels.

The Global Physical Activity Questionnaire (GPAQ) will be used to investigate the physical activity level of participants. The GPAQ is particularly well-suited for assessing habitual physical activity patterns in adults. Its structured format aligns closely with the typical daily activity profiles of adult populations, making it an appropriate tool for this study.

### Intervention

2.5

The intervention period will last for 12 weeks, with 3 supervised training sessions per week at the community fitness center. Each session will consist of a warm-up (5–10 minutes), a main exercise phase (30–60 minutes) on a treadmill, and a cool-down (3–5 minutes). To maximize training adaptations while ensuring safety, we have designed a progressive intensity protocol. Specifically, the MICT group will exercise at 45–55% of Heart Rate Reserve (HRR). The HIIT and LHIIT groups will perform high-intensity intervals (4-minute work intervals at 70–90% HRR separated by 3-minute active recovery intervals at 40% HRR) and the training load will be adjusted monthly in accordance with the CPET. The detailed progression of intensity and heart rate targets is presented in **Figure 2**.

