### Research design

2.1

This trial is a single-center, three-arm, open-label randomized controlled study (**Figure 1**). As a superiority trial, a non-exercise control group will not be included, given that numerous studies have already demonstrated the significant efficacy of aerobic training for decreasing HFC in individuals with MASLD. A total of 105 eligible participants aged 18–45 years will be randomized in a 1:1:1 ratio to the high-intensity interval training (HIIT) group, moderate-intensity continuous training (MICT) group, or low-volume HIIT (LHIIT) group. The intervention will last 12 weeks. The HIIT and MICT groups will perform exercise sessions aiming for approximately 400 kcal per session (~1200 kcal/week), while the LHIIT group will perform shorter sessions of approximately 200 kcal per session. To minimize confounding factors, all participants will receive standardized dietary guidance to maintain a stable caloric intake consistent with their baseline habits during the intervention period. All exercise sessions will be supervised by certified exercise trainers to ensure adherence, safety, and fidelity to the protocol. Due to the nature of the interventions, participants and trainers cannot be blinded; however, outcome assessors, imaging analysts, and statisticians will remain blinded to allocation. The primary outcome is the change in HFC, quantified by magnetic resonance imaging–proton density fat fraction (MRI-PDFF), with the primary comparison set between HIIT and MICT. Analyses involving the LHIIT group are considered exploratory and will be interpreted as hypothesis-generating. This trial protocol has been reviewed and approved by the Ethics Committee of the First Affiliated Hospital of Naval Medical University (CHEC2025-253) and registered on the Chinese Clinical Trial Registry (ChiCTR2500107821). Any modifications to the protocol will be fully documented and described in detail in subsequent publications.

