**Figure 2 f2:**
[figure not shown]
Exercise load. MICT, moderate intensity continuous training; HIIT, high-intensity interval training; LHIIT, low-volume high-intensity interval training; HRR, heart rate reserve.

To ensure precise energy matching, individual energy expenditure will be calculated based on physiological data obtained from the baseline CPET. An individual linear regression equation establishing the relationship between HR and VO_2_ will be generated for each participant. Based on this relationship, the target energy expenditure is calculated using the caloric equivalent of oxygen (~5 kcal/L), and the session time will be calculated by following formula.

$$Exercise\;time=\;\frac{Targeted\;energy\;consumption\left(kcal\right)}{Exercise\;VO_{2}\left(L\cdot min^{-1}\right)*5\left(kcal\cdot L^{-1}\right)}$$

For the HIIT protocol, the total number of cycles is calculated based on the energy expenditure per cycle, using the following formula. In the final cycle, the duration of both high- and low-intensity intervals will be proportionally adjusted to ensure accurate achievement of the total energy expenditure goal.

$$N_{\left(cycles\right)}=\;\frac{Targeted\;energy\;consumption\left(kcal\right)}{\left[VO_{2high}*4+VO_{2low}*3\right]\left(L\cdot min^{-1}\right)*\;5\left(kcal\cdot L^{-1}\right)}$$

N, total number of cycles.

To account for improvements in cardiorespiratory fitness and ensure the maintenance of the prescribed relative intensity, CPET will be repeated at Week 4 and Week 8. The exercise prescription (target heart rates and session duration) will be recalibrated based on these updated physiological parameters. During all training sessions, participants’ heart rates will be monitored in real-time using the Polar OH1(Polar, Finland).

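### The 30–60 minute main phase stated for every session cannot hold for both the 400 kcal MICT and the 200 kcal LHIIT prescription, and the schedule table omits the week 4 and 8 CPETs that reset session time

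*Protocol article*

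**What the plan says.** Section 2.5 (Intervention) describes each session as a warm-up, "a main exercise phase (30–60 minutes) on a treadmill", and a cool-down. It makes no exception by arm.

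Section 2.1 (Research design) says that the HIIT and MICT groups "will perform exercise sessions aiming for approximately 400 kcal per session", and that "the LHIIT group will perform shorter sessions of approximately 200 kcal per session". MICT is prescribed at 45–55% of heart rate reserve (HRR). HIIT and LHIIT alternate 4 minutes at 70–90% HRR with 3 minutes at 40% HRR.

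Section 2.5 then makes time an output. Each participant's linear HR–VO2 equation gives VO2 at the target heart rate, and session time, or the number of interval cycles, is the energy target divided by VO2 times 5 kcal/L. The same section states that "CPET will be repeated at Week 4 and Week 8", so that target heart rates and session duration can be recalibrated.

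Table 2, titled "The study schedule", marks cardiorespiratory fitness at screening, week 0 and week 12, with dashes at weeks 4 and 8.

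**The concern.** Session length is fixed in two ways: by a range of minutes and by an energy target. One session can satisfy both only if the range is wide enough for the VO2 values that the prescribed intensities imply. LHIIT has half the energy target of MICT at a higher average intensity, so its sessions must last less than half as long. A window whose upper end is exactly twice its lower end leaves no room for that.

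The stake is the primary comparison. HIIT against MICT can be read as an effect of intensity only if the two arms spend the same energy. A 60-minute limit would bind on the lower-intensity arm first, so any resulting mismatch runs in one direction.

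The schedule raises a second, separate question. The text relies on the week 4 and week 8 tests to update session time, and sites commonly work from the schedule table, where those tests do not appear.

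**Working it through.** **Inputs from the protocol.** Window 30–60 min (2.5); 400 kcal for HIIT and MICT, 200 kcal for LHIIT (2.1); MICT 45–55% HRR; intervals of 4 min at 70–90% and 3 min at 40% HRR; 5 kcal per litre of oxygen; an individual linear HR–VO2 relation; time = kcal / (5 × VO2) (all 2.5).

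**Step 1. VO2 implied by the window.**
- MICT, 400 kcal in at most 60 min: VO2 ≥ 400 / (60 × 5) = 1.333 L/min.
- LHIIT, 200 kcal in at least 30 min: mean VO2 ≤ 200 / (30 × 5) = 1.333 L/min.

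**Step 2. Mean intensity of an interval cycle.** (4 × 70 + 3 × 40) / 7 = 57.1% HRR; (4 × 90 + 3 × 40) / 7 = 68.6% HRR. This always exceeds MICT's 45–55%. Because VO2 is linear in heart rate, mean VO2 over the cycle is the VO2 at the mean heart rate. The proportional shortening of the last cycle leaves that mean unchanged.

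**Step 3. Combine.** On one rising line, LHIIT's mean VO2 is above MICT's. If MICT meets VO2 ≥ 1.333, LHIIT is above 1.333 and finishes in under 30 min. The 30–60 minute figure therefore cannot be reproduced for MICT and LHIIT together at any fitness level. This needs no outside VO2 value. A scan over resting VO2 0.15–0.50 and VO2peak 0.8–5.8 L/min found 0 of 135,000 combinations with all three arms inside the window. HIIT and MICT fitted together in 46,192 of them.

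**Step 4. Size, with assumed VO2 values.** The protocol gives none, so take resting VO2 0.25 L/min and VO2 = rest + f × (peak − rest), where f is the HRR fraction. At VO2peak 2.0:
- MICT: 0.25 + 0.45 × 1.75 = 1.0375 and 0.25 + 0.55 × 1.75 = 1.2125 L/min. Times 300 (60 min × 5), this gives 311 and 364 kcal.
- HIIT: 0.25 + 0.571 × 1.75 = 1.25 and 0.25 + 0.686 × 1.75 = 1.45 L/min. The first gives 375 kcal at 60 min; the second reaches 400 kcal in 55 min.

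The same steps for three fitness levels, with the range over the prescribed intensities:

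| VO2peak (L/min) | Time by formula, min: MICT / HIIT / LHIIT | Energy if held to 30–60 min, kcal: MICT / HIIT / LHIIT |
|---|---|---|
| 1.6 | 81–93 / 68–78 / 34–39 | 257–298 / 306–353 / 200 |
| 2.0 | 66–77 / 55–64 / 28–32 | 311–364 / 375–400 / 200–218 |
| 3.0 | 45–54 / 37–44 / 19–22 | 400 / 400 / 273–320 |

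**Step 5. Where HIIT and MICT both fit.** With resting VO2 0.25, MICT fits within 60 min from VO2peak 0.25 + (1.333 − 0.25) / 0.55 = 2.22 (at 55% HRR) or 2.66 (at 45% HRR). HIIT stays at 30 min or more up to 0.25 + (2.667 − 0.25) / 0.686 = 3.77 (at 90% HRR) or 4.48 (at 70% HRR). Moving resting VO2 over 0.20–0.40 shifts the MICT threshold only within 2.10–2.72 L/min.

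**Step 6. Schedule.** Section 2.5 has CPETs at weeks 4 and 8; Table 2 has dashes there. No arithmetic applies.

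**The case against.** The best defence is that Section 2.5 itself supplies the operative rule. Session time is calculated from the energy target, and the last interval cycle is adjusted to hit it. Section 2.1 already calls LHIIT sessions shorter, and no sentence calls 30–60 minutes a cap or a floor. On that reading matching is kept and the range is merely loose. This stands as a possible reading. It does not remove the conflict, because the range is stated for each session and one of the two statements must give way.

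A reader might infer that energy matching fails outright. The documents do not support that. Matching in this trial concerns HIIT and MICT, and both can reach 400 kcal inside the window at higher fitness (step 5). The impossibility at every fitness level arises only once LHIIT is included, and Section 2.1 declares LHIIT analyses exploratory. Nor should the MICT shortfall be measured against 400 kcal alone: at low fitness HIIT would be capped too, as the table shows.

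A reader might also infer that the missing Table 2 marks break the matching, or that a mismatch could never be detected. Neither follows. Section 2.5 states the recalibration plainly, and Section 2.4 introduces Table 2 as covering outcomes and their time points. Still, the table also lists consent, randomization, counselling and adverse events, so the absence of two prescribed tests is a real mismatch. As to detection, Section 2.8 scores adherence on attendance and intensity zone rather than on energy, but heart rate is recorded, so delivered energy can be computed.

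Figure 2 is not visible here and might give durations by arm. The text would still need correcting to agree with it.

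**Conclusion.** The point holds as an internal contradiction with a conditional consequence. The window, the two energy targets and the time formula cannot all be true. That result rests only on the protocol's own figures and its linear HR–VO2 assumption.

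The effect on the trial depends on which statement staff follow. Under the formula, the primary contrast stays matched. Under the window as a limit, MICT falls below HIIT for less fit participants. At the assumed VO2peak of 2.0 and rest of 0.25 L/min, the gap per session runs from 375 − 364 = 11 kcal to 400 − 311 = 89 kcal, or about 3% to 22% of HIIT's energy, always in HIIT's favour. How many participants fall in that range is unknown, since the protocol reports no VO2 values; Section 2.4.3.2 does describe compromised fitness as common in this population. The LHIIT excess at higher fitness touches only the exploratory comparison.

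The Table 2 discrepancy is a separate and smaller error of scheduling. Both should be corrected before sessions are prescribed.

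**What to change.** Reconcile the session window in Section 2.5, the energy targets in Section 2.1 and the time formula in Section 2.5, so that one stated rule governs session length in each arm. Reconcile Table 2 with the week 4 and week 8 CPETs. Which duration, energy target or testing schedule is right is for the investigators; none is proposed here.

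Whichever rule is kept, compute delivered kcal per session from the recorded heart rate and each participant's HR–VO2 equation, and report it by arm, so that the HIIT–MICT energy match can be verified.

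The cost is protocol wording, a correction to one table row, and some extra processing of data already collected. No new measurement is needed beyond the CPETs that the text already prescribes.

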**Figure 2 f2:**
[figure not shown]
Exercise load. MICT, moderate intensity continuous training; HIIT, high-intensity interval training; LHIIT, low-volume high-intensity interval training; HRR, heart rate reserve.

To ensure precise energy matching, individual energy expenditure will be calculated based on physiological data obtained from the baseline CPET. An individual linear regression equation establishing the relationship between HR and VO_2_ will be generated for each participant. Based on this relationship, the target energy expenditure is calculated using the caloric equivalent of oxygen (~5 kcal/L), and the session time will be calculated by following formula.

$$Exercise\;time=\;\frac{Targeted\;energy\;consumption\left(kcal\right)}{Exercise\;VO_{2}\left(L\cdot min^{-1}\right)*5\left(kcal\cdot L^{-1}\right)}$$

For the HIIT protocol, the total number of cycles is calculated based on the energy expenditure per cycle, using the following formula. In the final cycle, the duration of both high- and low-intensity intervals will be proportionally adjusted to ensure accurate achievement of the total energy expenditure goal.

$$N_{\left(cycles\right)}=\;\frac{Targeted\;energy\;consumption\left(kcal\right)}{\left[VO_{2high}*4+VO_{2low}*3\right]\left(L\cdot min^{-1}\right)*\;5\left(kcal\cdot L^{-1}\right)}$$

N, total number of cycles.

To account for improvements in cardiorespiratory fitness and ensure the maintenance of the prescribed relative intensity, CPET will be repeated at Week 4 and Week 8. The exercise prescription (target heart rates and session duration) will be recalibrated based on these updated physiological parameters. During all training sessions, participants’ heart rates will be monitored in real-time using the Polar OH1(Polar, Finland).

### Sample size

2.6

The sample size is calculated based on the primary comparison between the HIIT and MICT groups regarding the absolute change in MRI-PDFF from baseline to 12 weeks. Based on the previous study that implemented a similar intervention duration, we anticipated an absolute reduction in hepatic fat content of -1.7% (SD 1.1%) for the HIIT group and -0.9% (SD 0.7%) for the MICT group (22). Assuming a pooled standard deviation of 0.92% and a two-sided significance level of 0.05, a sample size of 28 participants per group is required to achieve 90% statistical power to detect the between-group difference. To account for a potential dropout rate of 20%, the sample size is adjusted to 35 participants per group. Consequently, a total of 105 participants will be recruited, with equal allocation (1:1:1) to the HIIT, MICT, and LHIIT groups.

